### Recruitment of participants

Since the intervention is designed to cater needs among local general working population, recruitment of participants is open to the public. Advertisement about the *Happy@Work* program is put up in relevant local magazines, websites, and other public space. Anyone who meets the eligibility criteria is welcome to participate. Furthermore, to maximize the recruitment efforts and to increase awareness among employers, we will also approach them directly, targeting consent from Human Resources managers to encourage staff to participate. More specifically, we have strategically teamed up with the Employers’ Federation of Hong Kong in the beginning, so that the Federation can recruit participants from its member organizations (mostly companies of large sizes). We will also contact small-medium enterprises associations and conduct workshops for specific companies through professional networks to further promote the program. During recruitment, we will highlight the potential benefits of the program, appealing to different audiences. For employers, we emphasize its effect on increasing morale and productivity, while reducing turn-over and medical cost; for individuals, we highlight the benefit of improving well-being and career development, while managing stress.

High dropout rate is a challenge often faced by web-based studies. We use several strategies and incentives to mitigate this problem: 1) Email reminders will be sent out to remind participants at different stages (e.g. upon availability of each training session) to adhere to the process and complete all trainings and assessments on schedule; 2) Conditioning on finishing all the assessments, an electronic certificate for participation will be awarded to participants who have successfully completed all four training sessions; 3) a HK$50 cash coupon will be offered to the first 500 participants (in either control or intervention group) who complete all the assessments.

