#### Control group

A waiting-list control condition will be employed. After the baseline assessment, the control group will receive a note informing them that they need to wait for four months before accessing the training materials. During the four-month waiting period, we will send email reminders to remind them to finish the post/follow-up surveys. As an incentive, the control group is also eligible to receive cash coupons upon completing all assessments.

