### Work engagement and ROI related measures

The Utrecht Work Engagement Scale - shorten version (UWES) [51] will be used to measure engagement. It is a 9-item self-rating scale with item scores from 0 to 6. It has an excellent internal consistency (e.g. Cronbach’s alpha varied between 0.85 to 0.92 across different samples from 10 countries [52]).

Work productivity changes will be measured by the WHO’s Health and Performance at Work Questionnaire - short form (HPQ) [53], which obtains information on individuals’ past 4 weeks productivity through assessing both absenteeism and presenteeism. It is currently unavailable in traditional Chinese. A standard ’translation and back-translation’ process was adopted to translate it into traditional Chinese [54]. We pre-tested the Chinese version before making further improvement.

The other two components for calculating the ROI besides work productivity are medical costs and time costs. To obtain these two measures, participants in both control and intervention groups will be asked to report the past-month medical expenditures and the share paid by their employers (if any); while the intervention group alone will also report time they spend on the entire trainings.

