### Data analysis

Results will be reported according to the Consolidated Standards of Reporting Trials (CONSORT) statement regarding eHealth [55]. The primary data analysis will follow the intention-to-treat principle and compare the differences in the above outcome measures between the intervention group and the wait-list control group. Because of the potential dropout, missing data is expected. When appropriate, we will use the expectation-maximization (EM) method to impute missing data [56]. In addition, per-protocol analysis will also be conducted.

The two groups will first be described in terms of their baseline characteristics. The primary data analysis will compare the effectiveness of *Happy@Work* in the intervention group with the changes in the control group, based on the differences on PsyCap-24, WEMWS, SWLS, CES-D and UWES. Repeated measures of ANOVA will be used to check the multivariate main effects of intervention (compared with control) and time (pre, post, follow-up), as well as their interaction effect. A two-sided P value of 0.05 or less will be considered as significant. We will compute the standardized effect size (Cohen’s d) as well. Moderator analysis will also be conducted to explore which sub-group/s would benefit more from the intervention, by regressing outcome variables on independent variables like age, gender, education and baseline CES-D scores. Work productivity change will be compared between these two groups as well. SPSS V.18 will be used for the data analysis.

To make the business case for similar type of interventions, return-on-investment of the program will be calculated from the employers’ perspective using the following formula:

ROI = (Gain from investment - Cost of investment)/Cost of the investment;

where, *Gain from investment* = total monetized value of employees’ work productivity gains + savings in employers’ share of medical cost; and

*Cost of investment* = Program designing and operation costs (assuming employers self-fund similar programs) + the monetized time cost (if employees use work time for the program training*).*

Self-reported monthly salary will be used to monetize the work productivity changes and time cost for each individual. All the afore-mentioned items will be the incremental value compared with the control group.

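### The ROI prices the whole between-arm difference in self-rated productivity at salary although participants know their arm, so a rating shift from known allocation is booked as employer gain

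*Protocol article*

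**What the plan says.** The comparator does nothing for four months and knows it. Under Control group: "A waiting-list control condition will be employed", and after baseline "the control group will receive a note informing them that they need to wait for four months before accessing the training materials". The other arm starts weekly training straight away. The article describes no masking and no attention control.

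Outcome assessment states that all measures are self-reported through the study website. The HPQ short form covers the past four weeks and measures "productivity through assessing both absenteeism and presenteeism" (Work engagement and ROI related measures).

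Data analysis defines ROI as (gain − cost)/cost. Gain is monetised productivity plus savings in the employer's share of medical cost. Cost is programme design and operation plus the time cost of training done in working hours. On valuation: "Self-reported monthly salary will be used to monetize the work productivity changes and time cost for each individual". All items are increments over the control group.

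Under Recruitment of participants, employers are approached "targeting consent from Human Resources managers to encourage staff to participate". The message differs by audience. To employers: "For employers, we emphasize its effect on increasing morale and productivity, while reducing turn-over and medical cost". To the people who will fill in the questionnaires: "for individuals, we highlight the benefit of improving well-being and career development, while managing stress".

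Strengths and limitations concedes recall bias and an ROI less objective than one from company records. It does not mention bias that differs by arm.

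**The concern.** Recall error that is the same in both arms largely cancels in an incremental comparison. Error that depends on the arm does not. Someone who has just completed a programme meant to help may rate their own performance a little higher, and someone told to wait may rate it a little lower. Both movements widen the HPQ difference, and the ROI formula converts that difference into salary without separating the component most open to judgement.

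A waiting list is a reasonable comparator for an employer choosing between the programme and nothing, provided that the measured gain is real work. The article intends a positive ROI to persuade employers to invest (Return-on-investment from employers' perspective; Future implementation). If much of that figure were a reporting shift, the business case would rest on something no employer receives.

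**Working it through.** **The plan's own figure.** The article states no expected ROI. Its only calculation is the sample size: effect 0.3 SD, 80% power, two-sided alpha 0.05. The normal formula gives 2 × (1.96 + 0.84)² / 0.3², rounded up to 175 per arm; the t version gives 176. The stated 177 reproduces within 2 and is not in dispute.

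**Inputs from the article**
- Four sessions of 15-30 minutes: 1-2 hours per participant, homework not counted (Intervention delivery).
- Working week of 49.6 hours (Background): 49.6 × 52/12 = 214.9 hours a month.
- ROI = (gain − cost)/cost (Data analysis).

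**Assumptions, because the article gives no figure**
- Presenteeism is a 0-10 rating with SD 1.5, and one point is worth 10% of salary.
- The true effect is zero, and knowing one's arm shifts the difference by 0.05-0.10 SD.
- The gain is credited for one month or, without decay, for four. The article states no crediting period. Each HPQ report covers four weeks.
- Programme cost per participant, c, is unknown and left free.

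**Step 1, time cost.** 1/214.9 = 0.47% and 2/214.9 = 0.93% of one month's salary.

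**Step 2, spurious gain per month.** 0.05 × 1.5 × 10% = 0.75%; 0.10 × 1.5 × 10% = 1.5%. Over four months: 3% and 6%.

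**Step 3, break-even programme cost.** With no true effect, ROI is above zero only if c < spurious gain − time cost.

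| Months credited | Shift | Spurious gain | Gain ÷ time cost | ROI > 0 only if c is below |
|---|---|---|---|---|
| 1 | 0.05 SD | 0.75% | 0.8 to 1.6 | −0.18% to 0.28% |
| 1 | 0.10 SD | 1.5% | 1.6 to 3.2 | 0.57% to 1.03% |
| 4 | 0.05 SD | 3% | 3.2 to 6.4 | 2.07% to 2.53% |
| 4 | 0.10 SD | 6% | 6.4 to 12.9 | 5.07% to 5.53% |

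Percentages are of one month's salary. A negative limit means that the shift does not even cover two hours of training. If training is done outside working hours, the time cost is nil and the limit equals the spurious gain.

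**Step 4, two worked values.** Take the 6% gain and two hours of training. At c = 2%, ROI = (6 − 2.93)/2.93 = +1.05. At c = 10%, ROI = (6 − 10.93)/10.93 = −0.45. The same shift gives either sign, depending on a cost that the article does not state.

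**Step 5, would a test reveal the shift?** With 177 per arm, the standard error in SD units is √(2/177) = 0.106. A shift of 0.05 or 0.10 SD reaches two-sided significance with probability 0.08 or 0.16, yet gives a positive point estimate with probability 0.68 or 0.83. The ROI uses the point estimate, so a shift that the significance test would usually miss still enters the total.

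**The case against.** Three stronger readings are tempting, and the article supports none of them.

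- *Recruitment biases the contrast.* A reader might infer this because productivity and medical cost, the two gain terms of the ROI, are what employers are told to expect. But the raters are told about well-being, career development and stress. The route through HR managers is indirect, and everyone hears the message before randomisation. Recruitment may prime expectations; known allocation makes them differ.
- *Expectancy alone would make the ROI positive.* The ratio of about 3 to 13 times time cost in the four-month rows invites this. It omits design and operation cost, which the article's formula includes, and it assumes four months without decay. With one month credited the ratio is about 0.8 to 3.2. The sign of the ROI is not shown.
- *Only absenteeism plus medical savings can be trusted.* Both are also self-reported by participants who know their arm, though they are less a matter of judgement. Making that tier a pass/fail condition would prevent a real presenteeism benefit from counting on its own, which changes what is being estimated.

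It is also fair to say that ROI is a secondary outcome, that a waiting list is common for such programmes, that the article concedes limited objectivity, and that ROI sensitivity analyses may sit in a fuller plan. Nor does anything show that the waiting note itself is worded in a leading way. What stands is narrower: the formula given in the article pools presenteeism into one monetised gain, and the stated limitations omit the bias that an incremental comparison does not remove.

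**Conclusion.** The concern holds in limited form. Controls know their allocation, all outcomes are self-reported, and the ROI gain takes the whole HPQ difference at salary value. A shift due to knowing one's arm is therefore counted as employer gain, probably in the programme's favour.

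Under the stated assumptions, that spurious gain is 0.75-1.5% of one month's salary for one credited month and 3-6% for four. The time cost is 0.47-0.93%, plus an unstated programme cost. Whether this alone would produce a positive ROI depends on programme cost and crediting period, and the article gives neither. The SD, the value per point and the size of the shift are illustrations, not figures from the article. The comparison of psychological capital can go ahead as planned; the point concerns the business claim.

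**What to change.** 1. **Data analysis.** Prespecify that ROI is reported both with and without the presenteeism component, from the HPQ data already collected. State that a positive ROI seen only when presenteeism is included will be described as dependent on unblinded self-ratings. Do not make the absenteeism-plus-medical figure a pass/fail gate.
2. **Strengths and limitations.** Name bias that differs by arm, and its likely direction, alongside recall bias.
3. **Recruitment of participants.** Where text can still be edited, say that the study tests whether the programme affects well-being and work, rather than presenting the benefits as established.

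The first two changes cost one extra line of output and a few sentences, and need no new data. The downside is a less favourable headline ROI and possibly slightly slower recruitment. Advertising and the employers' federation partnership are already under way, so the third change may be only partly achievable.

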### Description of intervention

#### Intervention content

*Happy@Work* is an individualized self-learning web-based program. The content of the intervention is designed based on a thorough literature review on PysCap [22,32-41]. It includes four training sessions, each targeting one of the four PsyCap components (Table 1): 1) hope, where a goal-setting training will be provided, mainly teaching individuals how to set up SMART (Specific, Measureable, Achievable, Relevant and Time-bound) goals [31-33]; 2) efficacy, an expressive writing training, which requires individuals to write about their personal feelings on their own work, past mastery experiences on work-related issues, etc. [35,42]; 3) optimism, which teaches individuals the ABCDE model (Adversity, Belief, Consequences, Disputation and Energization) of “learned optimism” [41]; and 4) resilience, where the risk management and resource leverage practice skills will be trained [31-33].

**Table 1 T1:** Content of the intervention program

**Components**	**Proposed training**
Hope	Goal setting (i.e. 1. Choosing of a personal goal; 2. Creating sub-goals; 3. Pathways generation; 4. Obstacle planning)
Efficacy	Expressive writing (i.e. adapted from existing guideline, basically requires individuals to write about their personal feelings on their own work; past mastery experiences on work-related issues; vicarious learning experiences; as well as the verbal persuasion experiences)
Optimism	Learned optimism (i.e. ABCDE model: 1) A stands for adversity; 2) B for the beliefs one automatically has when it occurs; 3) C for the usual consequences of the belief; 4) D for the disputation of individuals’ routine belief; 5) E for the energization that occurs when individuals dispute the belief)
Resilience	Risk management & Resource leverage practice (i.e. evaluating the risk for an adversity; practicing using different perspective to view it; planning strategies to control it; figuring out resources available and methods of getting more helpful resources; utilizing the resources to deal with the adversity)

In order to adapt the intervention to the local business and culture environment, we held a small focus group talking to four human resources managers of local companies (3 from large firms in banking, communication, and professional service, respectively and 1 from small-medium enterprises). We asked the managers to describe the key issues staff faces in the day-to-day operations, the common sources of stress or challenges, and what a “star” employee would be like. Based on the discussion, we developed cases for typical types of adversity local workers are expected to experience, thus demonstrate how each of the PsyCap component can be utilized.

#### Intervention delivery

A web-based format will be adopted to deliver the whole intervention and conduct assessment. Compared with traditional approaches, such as face-to-face counseling, a web-based approach has several advantages: 1) relatively cheaper; 2) once developed, it may be sustained and maintained with little cost to serve more people; 3) more flexible for individuals, in the sense that they can choose wherever or whenever to access the program; and 4) the web-based data collection would obviate data entry by the researcher (and associated human error). In terms of efficacy, one meta-analysis found that web-based instruction has similar effects as classroom instruction on teaching both declarative knowledge and procedural knowledge [43]. As for data quality, previous studies have shown that data collected via internet are just as diverse as data collected through traditional methods, and participants in web-based studies would treat the study the same or to provide accurate information as participants in traditional samples [44].

We worked with a web design vendor to combine the skill trainings and the localized cases through narrative technology such as flash animation. Each session is delivered in a pseudo-classroom setting, with the same trainer (an animated character) mainly providing the knowledge and guiding participants through the trainings. In addition to the participant, another animated character (different in each session) will act as the classmate who will present the specific case developed above as his or her own work challenge, and together with the participant, try to apply the skill learned. By providing such a role model for each session, we aimed to improve the learning efficiency of participants. Once participants start a session, the flash animation will automatically play by itself, with stops built in for either a “whiteboard” function or “check-point” questions. The “whiteboard” function is designed to display key knowledge/training points in a more self-controlled pace (with move-back or move-forward buttons); while the “check-point” questions (multiple-choice or brief answer questions) are built in as “breaks” during the class, which also allow participants to be tested on knowledge gained. Generally, it takes 15–30 minutes to complete each session. To better motivate participants, “happy coins” (virtual money value) are rewarded when they correctly answer the “check-point” questions or finish “homework”, the latter consists of post-session exercises participants can access after completing the training to reinforce skills learned.

Four training sessions are released one by one on a weekly base in a preset order (i.e. hope - efficacy - optimism - resilience), so that following each session individuals could have a week to practice the learned skills. A timer linked to each participant’s password-protected account is used to control individual progress. Upon completion of baseline assessment, the timer will start. Participants have up to a week to complete each training and practice the skills learned through accessing “homework”, and they can always revisit the previous sessions. Automatic email reminders will be sent out two days after a training session is available but not yet accessed. This is scheduled to help participants better follow through the whole intervention, which will take four weeks after baseline assessment.

#### Control group

A waiting-list control condition will be employed. After the baseline assessment, the control group will receive a note informing them that they need to wait for four months before accessing the training materials. During the four-month waiting period, we will send email reminders to remind them to finish the post/follow-up surveys. As an incentive, the control group is also eligible to receive cash coupons upon completing all assessments.

### Outcome assessment

The primary outcome is the level of psychological capital. The secondary outcomes include well-being, depressive symptoms, work engagement and economic cost-benefit (as measured by work productivity, medical expenditure and time cost for using the website). All these measures are self-reported, and will be collected through the *Happy@Work* website. Assessments will be made at the baseline, immediately after individuals finish the 4-week trainings, and at 1 and 3 months follow-up after the completion. All the measurements, except specified, will be assessed in both control and intervention groups.

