**Methods/Design:**

A two-arm randomized controlled trial design will be adopted. Eligible working adults will be randomly allocated to either the intervention group or the waiting-list control group, with 177 participants in each arm. The intervention, which consists of four web-based training sessions, each targeting one of the psychological capital components (hope, efficacy, optimism and resilience), will be implemented over a 4-week period. On-line surveys will assess the participants in each group at baseline, intervention completion, 1 and 3 months after the completion. The primary outcome is individuals’ psychological capital level; secondary outcomes include individuals’ well-being, depressive symptoms, work engagement and productivity. Return-on-investment will be calculated from the employers’ perspective based on productivity gain, savings in medical expenditure, as well as operation and time costs. Analysis will follow the intention-to-treat principle.

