## Methods/Design

### Study design

This study is designed as a two-arm randomized control trial. Upon visiting the intervention website, individuals will complete an initial screening to determine the eligibility. Eligible participants will continue the registration process and the baseline assessment, followed by an automatic randomization process that assigns the eligible participants into one of two groups. The intervention group will receive a 4-week access to *Happy@Work* trainings that develop each of the four PsyCap components. Measurements are scheduled at baseline, directly after the 4-week PsyCap trainings, and at 1 and 3 months follow up. The control group will be on the waiting list for 4 months before they can access the training materials. Figure 1 shows the flow of the study design.

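### Survey timing is worded around finishing the training, and control access opens only 0 to 3 days after the 3-month survey falls due

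*Protocol article*

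**What the plan says.** Three places in the protocol give the survey times.

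- Abstract, Methods/Design: "On-line surveys will assess the participants in each group at baseline, intervention completion, 1 and 3 months after the completion".
- Study design: "Measurements are scheduled at baseline, directly after the 4-week PsyCap trainings, and at 1 and 3 months follow up".
- Outcome assessment: the surveys come "immediately after individuals finish the 4-week trainings, and at 1 and 3 months follow-up after the completion".

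The Figure 1 legend requires the same three post-baseline surveys of both groups.

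On the training calendar, Intervention delivery says "Upon completion of baseline assessment, the timer will start". Sessions are released weekly, "Participants have up to a week to complete each training and practice the skills learned", and reminders help people "follow through the whole intervention, which will take four weeks after baseline assessment".

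On the control arm, Study design says "The control group will be on the waiting list for 4 months before they can access the training materials". The Control group section adds that controls are told of the wait after baseline and are reminded of their surveys by email while they wait. Demographics and other variables describes a question to controls about exposure over the preceding four weeks.

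Data analysis plans an intention-to-treat comparison by repeated-measures ANOVA with group, time and their interaction.

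**The concern.** Two things look wrong, and they are separate.

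First, the abstract and the outcome section count survey dates from finishing the training. Controls do no training in this period, and an intervention participant who skips sessions never finishes. The protocol expects substantial dropout and promises intention-to-treat, so both groups need a survey date that does not depend on completion. The account timer could supply one, but it is described as governing progress through the sessions, not the sending of surveys.

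Second, the control arm's access date sits almost on top of the last survey. Follow-up of controls depends on email reminders, so some late answers are foreseeable. A control who answers late may already have started the program. At stake is the 3-month between-group contrast, including that on the primary outcome, psychological capital.

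**Working it through.** **The plan's own figure.** The only calculated figure in the protocol is the sample size. For a standardized effect of 0.3, two-sided alpha 0.05 and 80% power, n per arm = 2 × (1.96 + 0.84)² / 0.3² = 174.2, so 175 (176 with the t distribution). The stated 177 agrees closely, and this point does not affect it.

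**Inputs for the calendar check**

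- Clock start: completion of baseline (Intervention delivery). The control wait is announced at the same point (Control group).
- Training period: 4 weeks = 28 days (Intervention delivery).
- Last survey: 3 months after that period (Study design, Outcome assessment).
- Control access: 4 months after baseline (Study design, Control group).
- Length of a month, m: not defined. I used calendar months over 365 consecutive baseline dates from 1 March 2014 (dates assumed), and the mean month of 30.4375 days.

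**Formulas, on the favourable reading that all surveys run from baseline**

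- 3-month survey due: D = 28 + 3m
- Control access: A = 4m
- Margin: A − D = m − 28

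**Results**

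| | Mean month | Calendar months: range (mean) |
|---|---|---|
| Survey due, D | 28 + 91.3 = day 119.3 | day 117–120 (119.2) |
| Access, A | day 121.75 | day 120–123 (121.7) |
| Margin | 2.4 days | 0–3 days (2.4) |

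If a month were counted as four weeks, D = 28 + 84 = 112 and A = 112, a margin of 0. On none of these conventions does access open before the survey is due, but an answer more than about 2 to 3 days late can come after access.

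**Other surveys.** The post-training survey is due at day 28 and the 1-month survey at about day 28 + 30.4 = 58. Access is then about 94 and 63 days away, so neither is exposed.

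**Size of the dilution.** Let p be the share of 3-month control answers given after access, and f the share of the full effect those controls have already gained. A true difference of 0.3 SD then appears as 0.3 × (1 − pf). Assume that sessions are also released weekly to controls (not stated for them) and that the effect builds evenly over the four sessions. In the first week after access f is then at most 1/4, and the loss is at most 0.3 × p/4 = 0.075p SD. For answers several weeks late f can rise toward 1 and the loss toward 0.3p. The protocol gives no figure for p.

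**The case against.** The strongest reply is that a common schedule can be read from the document. The timer starts at baseline, the course is fixed at four weeks, both groups take the same surveys, controls are reminded during their wait, and the four-week look-back suits a survey at week 4. On that reading completion simply means the end of the four-week period. This is probably the intent, and it carries weight.

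It defeats two stronger inferences that a reader might draw.

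- **That the arms are measured on different terms.** Taken literally, a person who finished 7 or 28 days late would have the 3-month survey at about day 126 or 147 (28 + 7 + 91.3 or 28 + 28 + 91.3), against 119 for a control. But the sessions follow a weekly timetable within a four-week course, so the document does not support assuming such drift.
- **That only finishers are surveyed, which would defeat intention-to-treat.** Nothing withholds surveys from non-finishers. Recruitment of participants ties the cash coupon to assessments alone and the certificate to assessments and sessions as separate conditions. Interviews are planned with people who quit, and Data analysis expects missing data. A selection bias cannot be sized either. No finishing rate is given, and the planned group-by-time analysis compares change, so a raw difference in post-training scores would not describe it.

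A second reply is that survey windows and login rules are operational details that an article leaves to the full protocol. That is fair for the windows. The anchor, however, is not left out: it is stated, in words that do not fit controls or non-finishers. The four-month wait is also stated, and the thin margin follows from it.

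A third reply is that the contamination is small and conservative. That stands, and it limits the weight of the point.

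**Conclusion.** The concern holds in a limited form. The survey-timing wording is ambiguous for controls and non-finishers, although the rest of the protocol suggests a common schedule from baseline. On that schedule controls gain access 0 to 3 days (mean 2.4) after the 3-month survey falls due, with no stated condition that the survey comes first. Late control answers could therefore dilute the 3-month contrast. The effect is a bias toward the null at the last survey only. It is slight for answers a few days late and larger only if many controls answer weeks late.

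The margin rests on the protocol's stated intervals and on ordinary calendar months. The dilution bound rests on the assumed weekly release to controls and an evenly accruing effect. The finding does not show that the arms are measured differently or that intention-to-treat fails. It is a cheap correction, not a fatal flaw.

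**What to change.** 1. State that all surveys in both arms are timed from the baseline/randomisation timer, at 4 weeks, 4 weeks + 1 month and 4 weeks + 3 months, and go to every participant whatever number of sessions was completed. Use this wording in the abstract, Study design and Outcome assessment.
2. Have the website present the 3-month survey to controls before any training page can be opened.
3. Keep any control answer given after training access in the primary intention-to-treat analysis, and examine its exclusion only as a sensitivity analysis. Setting such answers to missing in the primary analysis would add missing data in one arm only, on the basis of behaviour after randomisation.

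The cost is a few words of text, a website setting on the existing account system and one sensitivity analysis, with no added visits or data. The one downside is a possible short delay in access for controls who have not yet answered.
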